**Discussion:**

The primary hypothesis of this study is that an excessive reduction in serum lipid levels by an intensive statin therapy in AIS patients with CMBs can increase the risk of intracranial hemorrhage. This study will shed light on new clinical decisions regarding the long-term serum lipid management in these patients with dilemma in clinical practice.

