### Randomization and blinding

All patients who are undergoing an AIS will be screened timely according to inclusion and exclusion criteria by a qualified investigator of each center. Then the eligible patients will be randomized into high-dose and low-dose atorvastatin arms in a 1:1 ratio (Figure 1). The concealment of allocation will be performed using sealed envelopes with numbers by the participants' physicians. Considering the non-subjective nature of the primary outcomes, as well as the reason that the investigator-initiated clinical trial without technical and financial support from any pharmaceutical manufacturer to develop placebos that meet the study design requirements in clinical practice, the study finally gave up the design and application of placebo, and only designed a single-blind manner for the study investigators. So, it's important to note that neither the participants nor their physicians conducting the drug intervention can be blind to the grouping, because the number of tablets administered in different groups will be different, so these physicians cannot be involved in the research process. All investigators and data collectors will not participate in the whole intervention.

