### Sample size estimates

Sample size calculations were based on the primary outcomes (the incidence of ICH). All participants are expected to be enrolled for 1 year and followed for 36 months. It will be tested whether the high-dose statin arm suffers a higher risk of hemorrhage than the low-dose statin arm in terms of the primary outcomes for 36 months. According to the SPARCL trial (the incidence of ICH: 25.2 vs. 12.0% in high-dose statin arm vs. low-dose statin arm with 4.9 years of mean follow-up duration) (17). The sample size was calculated by PASS software (version 15.0) with a two-sided type I error of 5% (α = 0.05) and 80% power, a sample size of 137 patients in each arm is required (total 274 patients). Assuming around 20% loss to follow-up, a total of 344 patients will be randomized.

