### Statistical analysis

SPSS 25.0 software will be used for statistical analysis by data analysts who are blind to the study. Two-sided *P*-values will be calculated with a significant level of 5%, and the parameters will be estimated by 95% confidence intervals. The primary analysis will be under intention-to-treat (ITT) principle and be performed on both the ITT population and per-protocol (PP) population.

Descriptive statistics of demographic data and other baseline eigenvalues will be performed on the ITT population for both groups. Continuous variables will be presented as mean (SD) or median (IQR). Categorical variables will be presented as numbers (%). For continuous variables and categorical variables, *t*-test/rank sum test and chi-square test/Fisher exact test will be used to detect possible disequilibrium between groups.

The outcomes will be performed on both ITT and PP population. Initially, the number and percentage of HS cases and patients with mild-to-severe CMBs at baseline and annul follow-up will be calculated and compared between the two arms by Chi-square test or Fisher's exact test. Then, for all time-to-event models, cumulative event rate during the follow-up will be estimated using the Kaplan-Meier method and will be compared with the log-rank test. If needed, Cox proportional hazard regression analysis will be used after testing proportional hazard assumption and important potential covariates will be adjusted for sensitivity analyses. The mean and variability of serum lipid levels in 36 month follow-up with at least three measurements will be calculated and compared by Student *t*-test or Wilcoxon rank sum test. Then generalized linear mixed model will be used to analyze the correlation between the proportion of CMBs with different degrees and serum lipid levels over time.

The interim analysis will be performed when 172 subjects have completed at least one follow-up SWI, and it will be focused on subject recruitment, comparability of baseline between groups, sample size assumptions to account for event incidence, follow-up shedding rate, adverse event data, and the effect of treatment on the primary and secondary outcomes.

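### The co-primary change in CMB degree is ordered and its hypothesis is directional, but the only arm comparison stated for it is an unordered chi-square or Fisher test on degree at each visit

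*Protocol article*

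**What the plan says.** The Primary outcomes section gives two parts: the incidence of hemorrhagic stroke (HS), and the change in CMB degree to the end of the 36-month follow-up. The hypothesis in the Abstract (Discussion paragraph) has a direction: intensive lowering "can increase the risk of intracranial hemorrhage", a term that the Aim paragraph defines to include CMBs.

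The Statistical analysis section puts both parts under one test. Counts and percentages of HS cases, and of patients with CMBs graded from mild to severe, at baseline and at each annual visit, are to be "compared between the two arms by Chi-square test" or by Fisher's exact test. The only other model that uses CMB degree is a generalized linear mixed model for "the correlation between the proportion of CMBs with different degrees and serum lipid levels over time". It relates degree to lipids; arm is not its stated term of interest. A rank-sum test appears in the section, but only for baseline variables and lipid levels.

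The sample size rests on the incidence of intracranial hemorrhage (ICH) alone. The article states no power, grade cut-offs or expected effect for CMB degree.

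**The concern.** A scale that runs from mild to severe is ordered. The comparison cannot simply be presence against absence, because CMBs on baseline imaging are an inclusion criterion and presence at baseline is therefore 100% in both arms. What can be compared is degree.

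With three or more degrees, Pearson's chi-square and Fisher's exact test give the same P-value whichever way the columns are arranged. They spread their sensitivity over every pattern of difference, including patterns with no clear direction (more moderate and fewer severe, for example). The trial asks whether the high dose is worse. A significant result says only that the two distributions differ, and a consistent shift toward worse degrees is detected less often than by a test aimed at it. The test is also applied to degree at each visit, whereas the outcome is change in degree.

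**Working it through.** **1. The plan's own figure.** Inputs from Sample size estimates: "the incidence of ICH: 25.2 vs. 12.0% in high-dose statin arm vs. low-dose statin arm", "with a two-sided type I error of 5% (α = 0.05) and 80% power". Formula (pooled variance under the null, no continuity correction):

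n = [1.960 × √(2 × p̄ × (1 − p̄)) + 0.842 × √(p1(1 − p1) + p2(1 − p2))]² / (p1 − p2)²

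With p̄ = 0.186, this is [1.960 × 0.5503 + 0.842 × 0.5423]² / 0.132² = 2.356 / 0.01742 = 135.2, so 136 per arm. The article states "a sample size of 137 patients in each arm is required (total 274 patients"; at 137 the power is 80.5%. Dividing 137 by 0.8 gives 171.25, so 172 per arm and 344 in all, as stated. The figure reproduces to within one patient, but it belongs to ICH incidence. Below, 137 per arm is borrowed only as a plausible evaluable number.

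**2. One worked case (assumed inputs).** Assume three grades, 50/30/20% in the low-dose arm, and a common odds ratio (OR) of 1.8 toward worse degrees.
- Low-dose cumulative odds are 0.5/0.5 = 1 and 0.8/0.2 = 4. Divided by 1.8 they are 0.556 and 2.222, so the high-dose arm is 35.7/33.3/31.0%.
- Non-centrality of Pearson's test: λ = (n/2) × Σ d²/p̄, where d is the arm difference and p̄ the average in each grade. This is 68.5 × (0.1429²/0.4286 + 0.0325²/0.3163 + 0.1103²/0.2552) = 68.5 × 0.0987 = 6.76. The sum is the same for any ordering of the grades.
- Non-centrality of a rank-score test: λ = (n/2) × (Σ d × r)² / var(r), where r are the mid-ranks of the pooled distribution. This is 68.5 × 0.0847² / 0.0728, which is 6.76 before rounding.
- The signal is the same, but Pearson's test uses 2 degrees of freedom and the ordinal test 1. Power is 63.9% against 73.9%, and chi-square needs about 170 per arm to match.

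The same 50/30/20% distribution gives 44.5% against 54.8% at OR 1.6, and 78.8% against 86.5% at OR 2.0.

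**3. How far this depends on the assumptions.** Simulation, 20,000 trials per row, 137 per arm, chi-square against Wilcoxon:

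| Low-dose distribution (%) | OR | Chi-square | Wilcoxon | Difference (points) |
|---|---|---|---|---|
| 60/25/15 | 1.5 | 32.0% | 40.5% | 8.5 |
| 60/25/15 | 1.75 | 56.4% | 67.4% | 11.0 |
| 60/25/15 | 1.9 | 69.7% | 79.2% | 9.5 |
| 60/25/15 | 2.5 | 95.7% | 98.0% | 2.3 |
| 70/20/10 | 1.9 | 64.5% | 74.6% | 10.1 |
| equal thirds | 2.5 | 96.1% | 98.1% | 2.0 |
| 10/50/25/15 | 1.75 | 52.8% | 69.6% | 16.8 |
| 10/50/25/15 | 2.5 | 94.4% | 98.2% | 3.8 |

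With two categories both tests have 1 degree of freedom and nothing is lost.

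**4. Shifts without a common odds ratio** (low dose 60/25/15%, 137 per arm):

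| High-dose distribution (%) | Pattern | Chi-square | Wilcoxon |
|---|---|---|---|
| 45/40/15 | lowest to middle grade only | 70.5% | 52.2% |
| 60/12/28 | middle to highest grade only | 88.4% | 13.7% |
| 50/40/10 | non-monotone | 68.2% | 18.0% |

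Here the advantage reverses. The first two patterns are genuine worsening.

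**5. Type I error.** With 60/25/15% in both arms, chi-square rejects in 4.9% of simulated trials and Wilcoxon in 4.85%. Both hold the nominal 5%.

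**The case against.** The other side has several fair points.

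- **No fixed power loss can be quoted.** A reader might infer that the plan gives up about 10 points of power. The documents do not support that as a fact about this trial. They give no grades, distribution, CMB effect or CMB power, and the figure needs three grades and a moderate common odds shift. This stands.
- **The ordinal test is not always stronger.** For worsening confined to one grade, chi-square can have clearly more power, as step 4 shows. So it cannot be said that any true worsening is missed more often. This stands.
- **Change may be scored in two categories.** If each patient is classed as progressed or not, the table is 2 × 2 and nothing is lost. The article does not say how change will be tabulated. This stands, and it limits the point to three or more ordered categories.
- **Direction will be visible.** Percentages per arm will be reported, and the section promises 95% confidence intervals. This softens the harm, but the test supplies no single estimate to which an interval could attach.
- **The test is only a first step.** The section introduces it as an initial comparison, and a full protocol or analysis plan may say more. However, none of the later steps described gives a clear arm contrast for CMB degree: the survival methods are for time-to-event models and the mixed model concerns lipids. The objection therefore answers little. The choice of test for a co-primary outcome is stated, not left open.

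**Conclusion.** The point holds as a weakness in efficiency and interpretability. An ordered co-primary outcome with a directional hypothesis has, as its only stated arm comparison, a test that ignores order, gives no single effect estimate or direction, and is applied to degree at each visit.

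A reader might go further and infer that the P-value would be invalid. It would not, since type I error is kept. The mixed model is not a second instance of the fault, because it does not compare the arms.

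The size is conditional. Under a common odds shift with ORs of 1.5 to 2.5 and 137 per arm, the loss is about 2 to 11 points with three grades and up to about 17 with four. It is zero with two categories, and the sign can reverse for shifts confined to one grade or for non-monotone shifts. The number of grades, their distribution and the effect are all assumptions. The case for change rests as much on having a directional estimate as on power.

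**What to change.** Define the CMB grades, and make the arm comparison an ordinal analysis of 36-month degree adjusted for baseline degree. This can be a proportional-odds model with arm as the term of interest, reporting one common odds ratio with its 95% confidence interval, or a rank or trend test stratified by baseline degree. The baseline term is needed because the outcome is change. Show the raw table of degrees by arm beside the estimate, and keep chi-square or Fisher for the binary HS outcome.

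The cost is a few sentences of analysis text, with no added patients or assessments. The downside is that the summary relies on a roughly common odds ratio across grades, and the test has less power against a shift confined to one grade; the raw table lets a reader see such a pattern.

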## Introduction

Cerebral microbleeds (CMBs) are a crucial radiological marker of cerebral small vessel disease (CSVD) (1) to illustrate the micropathology of perivascular hemosiderin deposition corresponding to past small foci of bleeding (2). The prevalence of CMBs increases with age and exceeds 20% in community population over 60 years old (3, 4). More importantly, CMBs are also a common comorbidity of stroke, brain trauma, Alzheimer's disease, and cerebral amyloid angiopathy (5, 6), and are associated with cognitive impairment, psychiatric symptoms, and decline of daily living ability (7).

CMBs have been identified to be indicative of bleeding-prone microangiopathy for their dynamical accumulation over time, with the burden (presence and number) of baseline CMBs predicting the development of new CMBs in both deep and lobar regions, and may predict spontaneous intracranial hemorrhage (ICH) (8–12). These pieces of evidence have suggested an important link between the presence of CMBs and future macrobleeding. However, CMBs have also been demonstrated in approximately one-third of patients with ischemic stroke (IS), that are associated with an increased risk of recurrent IS, symptomatic ICH and death (13). As the burden of CMBs in IS patients increased, the relative and absolute risk ratios for ICH increase steeply, although the absolute incidence of recurrent IS is consistently higher than that of ICH (13–16). Therefore, it raises clinical dilemmas, particularly regarding the safety of secondary prevention treatment of IS with concomitant presence of CMBs.

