#### Secondary outcomes

The incidence of recurrent IS and TIA.

The incidence of myocardial infarction.

The incidence of cardiovascular death.

The incidence of adverse events.

The incidence of all-cause mortality.

The mean of serum lipid levels [TG, TC, LDL-C, and high-density lipoprotein cholesterol (HDL-C)] for 36 months with at least 3 measurements.

The variability of serum lipid levels (TG, TC, LDL-C, and HDL-C) for 36 months with at least 3 measurements.

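### The primary haemorrhagic stroke outcome has two between-arm tests with neither named as decisive, and the first-listed one ignores follow-up time although 20% loss is planned

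*Protocol article*

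**What the plan says.** All of this is in the protocol article. Under Primary outcomes, the first part of the co-primary outcome is the incidence of HS on CT or MRI.

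The Statistical analysis section gives that outcome two comparisons in sequence:

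- **Percentages.** "Initially, the number and percentage of HS cases and patients with mild-to-severe CMBs at baseline and annul follow-up will be calculated". The arms are tested against each other by chi-square or Fisher's exact test.
- **Time to event.** The next step reads: "cumulative event rate during the follow-up will be estimated using the Kaplan-Meier method and will be compared with the log-rank test". It covers every time-to-event model.

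A model comes third and is conditional: "If needed, Cox proportional hazard regression analysis will be used after testing proportional hazard assumption". The adjustment covariates are not named and are assigned to sensitivity analyses. The primary analysis follows intention to treat (ITT), and outcomes are also analysed per protocol.

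Other sections bear on the choice:

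- Sample size estimates plans for about 20% loss over 36 months.
- Randomization and blinding says that patients and treating physicians know the allocation.
- Secondary outcomes lists "The incidence of all-cause mortality" separately, with no expected rate.
- The Introduction says that as microbleed (CMB) burden rises in ischaemic stroke, "the relative and absolute risk ratios for ICH increase steeply".
- Participants admits patients with any number of CMBs.

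**The concern.** Two p-values for one primary outcome, with no order of precedence, leave the conclusion open when they disagree. They are most likely to disagree when follow-up differs between arms. That is a realistic possibility here: one arm takes four tablets a night and the other one, and neither patients nor treating physicians are blind. The trial's hypothesis is one of harm. If the high-dose arm loses more patients, a percentage over all randomised patients shrinks the excess it is meant to detect. If the low-dose arm loses more, it exaggerates that excess.

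The second issue is estimation. The trial is meant to inform the balance between haemorrhage and ischaemic benefit, so absolute risks matter. Kaplan–Meier is named as the estimator of the cumulative event rate in patients aged up to 90 followed for three years. If deaths are censored, its complement describes HS risk in a population in which nobody dies of anything else.

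A lesser issue is that the strongest prognostic factor the article itself identifies is not fixed as a covariate, although baseline SWI is obtained in every patient.

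**Working it through.** **1. The plan's own figure.** Inputs from Sample size estimates: 25.2% vs 12.0%, two-sided α 0.05, power 80%. With pooled proportion 0.186:

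n = [1.96·√(2·0.186·0.814) + 0.8416·√(0.252·0.748 + 0.12·0.88)]² / 0.132² = (1.0786 + 0.4564)² / 0.017424 ≈ 135.2, so 136 per arm (stated: 137).

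137/0.8 = 171.25, so 172 per arm and 344 in total, as stated. The trial was sized for a comparison of two proportions.

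**2. Risks at 36 months.** The stated rates refer to 4.9 years. Assuming a constant hazard, 1 − 0.748^(3/4.9) = 16.3% and 1 − 0.88^(3/4.9) = 7.5%. The yearly hazards are 0.0593 and 0.0261. These are illustrative values only.

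**3. Effect of loss on the percentage.** Assume exponential loss and that lost patients count as event-free. With loss hazard c = −ln(1 − loss)/3, the observed proportion is λ/(λ + c)·[1 − exp(−3(λ + c))].

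- Loss 20%/20% (c = 0.0744): 14.6% vs 6.8%. The difference is 7.9 points instead of 8.8.
- Loss 30% high-dose, 10% low-dose: 13.8% vs 7.1%. The difference is 6.6 points.

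**4. Effect on the tests.** I simulated 20,000 trials of 172 per arm with exponential times. Ranges cover no deaths and 10% deaths per arm. Type I error is with 16.3% HS risk in both arms.

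| Loss, high/low dose | Chi-square power | Log-rank power | Tests disagree (true difference) | Type I error if either test counts |
|---|---|---|---|---|
| 20%/20% | 65–67% | 65–67% | 3–4% | 5.7% |
| 25%/15% | 58–60% | 65–67% | 7% | 6.7–7.0% |
| 30%/10% | 51–53% | 65–67% | 14% | 8.6–8.8% |

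Log-rank alone holds about 5% throughout. Chi-square alone rises to about 7% at 30%/10%. With 7.5% HS risk in both arms, the either-test error at 30%/10% is about 7%; with the stated 25.2% in both arms it is about 10.5%.

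**5. Kaplan–Meier as absolute risk.** If deaths are censored, 1 − KM estimates 1 − exp(−3λ). The actual cumulative incidence is λ/(λ + d)·[1 − exp(−3(λ + d))], with d = −ln(1 − mortality)/3. For the high-dose arm (1 − KM = 16.3%):

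| Assumed mortality | Cumulative incidence | Excess of 1 − KM |
|---|---|---|
| 10% | 15.5% | 0.8 points |
| 15% | 15.1% | 1.2 points |
| 20% | 14.6% | 1.6 points |

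In the low-dose arm the excess is 0.4 to 0.8 points.

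**6. Adjustment for CMB grade.** In 2,000 simulated trials with assumed hazards of 1:2:5 across three grades, power was 61.3% for unadjusted Cox, 63.8% for adjusted Cox and 63.7% for chi-square. The gain within the Cox model is about 2.5 points. There is none over chi-square.

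**7. Room for covariates.** Expected HS events are 172 × (0.1465 + 0.0676) ≈ 37. Arm (1), three-level grade (2) and five centres (4) make seven parameters, or about five events each.

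**The case against.** The case against is substantial, and much of it stands.

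- **A reader might infer that both analyses mishandle loss and death.** They do not. Kaplan–Meier and log-rank handle non-informative loss correctly. Log-rank with deaths censored is a valid test of the cause-specific hazard, just as a cause-specific Cox model is. Only 1 − KM read as absolute risk is open to criticism. The weakness of the percentage comparison is loss, not death.
- **The article does not say how lost patients or deaths are counted.** Counting the lost as event-free and censoring deaths are conditional readings. An unseen analysis plan may settle both.
- **A reader might infer that CMB burden is adjusted for only when needed.** In the text, "If needed, Cox proportional hazard regression analysis will be used" governs the model. CMB burden is neither included nor excluded. An unadjusted comparison in a randomised trial is valid, so leaving it out is not a bias.
- **With equal loss little is at stake for the test.** The two tests have the same power, and accepting either gives 5.7%. Larger effects need unequal loss, which is assumed here.
- **Mortality may be low.** Exclusions cover life expectancy under three years, malignancy, severe stroke and prior dependence.
- **The order of the text and the two-proportion sample size hint that percentages are the planned basis.** That is a fair inference, but the article does not say so. If it is right, the deciding test is the one more exposed to loss.

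What the objection does not remove is that two tests of a primary outcome are written down with no statement of which one decides.

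**Conclusion.** The point holds in a limited form. The firm part rests on the text alone: HS has two between-arm tests, neither is designated, and the first ignores follow-up time in a trial that plans for 20% loss.

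The size depends on assumptions. With equal loss, the observed percentages are about 10% too low in relative terms and the tests behave alike. With 30% vs 10% loss, chi-square loses about 14 points of power relative to log-rank, and choosing between tests takes type I error to about 9%. Arm-specific loss, exponential times, non-informative loss and the conversion of the 4.9-year rates to 36 months are all assumed.

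The absolute-risk point is smaller (0.8–1.6 percentage points in the high-dose arm) and applies only if deaths are censored and mortality is 10–20%. The same applies in kind to recurrent stroke, myocardial infarction and cardiovascular death.

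The covariate point is minor: it concerns prespecification and a small gain in precision, not validity.

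**What to change.** - **Primary HS test.** Name one ITT time-to-event analysis: log-rank or a cause-specific Cox model. State how losses and deaths enter it.
- **Percentages.** Keep the table of HS numbers and percentages as description, without a deciding p-value.
- **Absolute risk.** Report cumulative incidence by the Aalen–Johansen estimator, with death as a competing event. For cardiovascular death the competing event is non-cardiovascular death.
- **Adjustment.** Prespecify baseline CMB grade as the adjustment covariate in place of the conditional wording. With about 37 expected events, do not add centre as fixed effects.

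The cost is wording: the outcomes, deaths and baseline SWI are already collected. One downside is that the competing-risk estimator may need software beyond the SPSS 25.0 that the article names. The other is that the stated sample size was derived for two proportions, so the text should say that the primary test now differs from the sizing test. On the stated rates, the log-rank requirement is similar (about 253 to 280 patients, against 274).

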### Treatment

High-dose atorvastatin arm: Atorvastatin calcium tablets four pills (80 mg), quaque nocte (24 ± 1 h between two doses), orally, until the end of follow-up.Low-dose atorvastatin arm: Atorvastatin calcium tablets one pill (20 mg), quaque nocte (24 ± 1 h between two doses), orally, until the end of follow-up.

It is strongly recommended in both arms for the optimal treatment including acute treatment and other secondary prevention agents in accordance with clinical practice guidelines and the best medical conditions in the health care unit.

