### Follow-up

Detailed follow-up schedules and procedures are provided in Figure 1. Baseline characteristics, SWI and clinical laboratory tests will be obtained at enrollment. The following assessments will be performed at 1 month and annually follow-up: blood tests, SWI, study compliance, concomitant medication, adverse events, and withdrawal criteria. As it is not clear whether participants in this study would benefit more from following current guidelines or moderately relaxed lipid management targets. No further interventions which might violate the study protocol should be taken (such as suggesting withdrawal from the study or adjusting the treatment plan, etc.) if it is found that the serum lipid levels of the participants do not meet the current guidelines either for both groups. But the participants' doctor should be informed to strictly monitor their lipid levels and clinical conditions.

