In addition, in the secondary prevention of IS, national guidelines around the world delineate different lipid regulation criteria for different baseline conditions, emphasizing the use of high-intensity or maximum tolerated doses of statins to achieve serum LDL-C < 1.8 mmol/L (70 mg/dl) and/or a ≥50% reduction from baseline in those most likely to benefit (25, 26). However, current clinical studies and practice guidelines have failed to suggest lower limits for lipid management goals. Several studies have confirmed that lower serum TG, TC, and LDL-C levels increased the risk of CMBs (17, 19, 24, 27), and the presence of CMBs was associated with increased subsequent ICH risk and poor functional prognosis in patients with AIS (28). These studies suggest that unlimited reduction of serum major lipid levels, mainly LDL-C, is likely to be detrimental in the secondary prevention of IS, especially in IS with CMBs. Therefore, further studies are urgently needed to explore the safe lower limits of lipid management goals in IS with CMBs.

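### The only repeated-measures model for CMBs relates degree to lipid level, not randomised arm, and a shared time trend alone could make lower lipids appear to go with more CMBs

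*Protocol article*

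**What the plan says.** The Statistical analysis section gives CMB degree two treatments.

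- A between-arm comparison, planned alongside the one for HS: "patients with mild-to-severe CMBs at baseline and annul follow-up will be calculated and compared between the two arms by Chi-square test or Fisher's exact test". No adjustment for baseline CMB burden is mentioned, and each visit appears to be tested separately.
- A longitudinal model: a "generalized linear mixed model will be used to analyze the correlation between the proportion of CMBs with different degrees and serum lipid levels over time". Lipid level is the explanatory variable. The sentence lists no fixed effects, lag or covariates.

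The data come from the Follow-up section. At entry, "Baseline characteristics, SWI and clinical laboratory tests will be obtained at enrollment". After that, "The following assessments will be performed at 1 month and annually follow-up: blood tests, SWI". Under Treatment, every patient takes atorvastatin, 80 mg or 20 mg nightly, until follow-up ends.

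The Abstract states the hypothesis in terms of lipids: "an excessive reduction in serum lipid levels by an intensive statin therapy in AIS patients with CMBs can increase the risk of intracranial hemorrhage". The main Discussion likewise attributes bleeding risk to how far lipids fall rather than to statin use itself, and adds that "further studies are urgently needed to explore the safe lower limits of lipid management goals in IS with CMBs".

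**The concern.** The Introduction describes CMBs as accumulating over time, and the trial treats both arms with a statin from enrolment. Lipids should therefore be highest at baseline, when CMB burden is lowest, and lower at every later visit, when burden is equal or higher. A repeated-measures model with lipid as its only predictor would read that before-and-after pattern as an association, whether or not lipids matter.

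Two further problems remain once time is handled. The assigned dose determines much of the post-baseline lipid level, so a dose effect that does not act through lipids would appear as a lipid effect. Lipid level also reflects adherence, illness and patient characteristics, so patient-level confounding can act in either direction.

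The hypothesis is worded as lipid reduction, so readers would naturally take this model as its test, and the time artefact points the way the hypothesis predicts. Meanwhile the randomised comparison of the same outcome uses visit-by-visit tests that do not use the baseline CMB burden already collected.

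**Working it through.** The disputed sentence contains no figure to reproduce. The sample size, used below only as an input, follows from the article: 137 / 0.80 = 171.25, rounded up to 172 per arm, and 2 × 172 = 344.

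**Why time dominates the lipid variation.** Assume baseline LDL-C of 2.9 mmol/L and falls of 50% (80 mg) and 37% (20 mg). These are assumptions; the article gives no lipid values.

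- Follow-up LDL-C: 2.9 × 0.50 = 1.45 and 2.9 × 0.63 = 1.83 mmol/L.
- Fall from baseline: 1.45 and 1.07 mmol/L, mean 1.26.
- Difference between arms after baseline: 1.83 − 1.45 = 0.38 mmol/L.

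The before-and-after fall is about three to four times the between-arm difference (1.07 / 0.38 = 2.8; 1.45 / 0.38 = 3.8). Now let the log-odds of a higher CMB grade rise by 0.3 per year from time alone. Follow-up visits at 1/12, 1, 2 and 3 years average 1.52 years, so log-odds rise by 0.3 × 1.52 = 0.46. The before-and-after contrast alone gives a spurious slope of −0.46 / 1.26 = −0.36 per mmol/L. An arm term leaves this in place because both arms share it; a visit term absorbs it.

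**Simulation 1.** 344 patients, 1:1, visits at 0, 1, 12, 24 and 36 months, baseline LDL-C SD 0.6, patient random-effect SD 1.5, true lipid effect zero, 400 runs per scenario. The model was logistic for higher grade on concurrent LDL-C with patient-clustered standard errors, standing in for the mixed model. Assumed log-odds slopes: time trend 0.3 per year, non-lipid effect of the higher dose 0.4 per year. Entries are the percentage of runs with a significant negative lipid coefficient (nominal 2.5%).

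| Scenario | Lipids only | + visit | + visit, arm, arm-by-visit | + baseline lipid as well |
|---|---|---|---|---|
| Nothing links lipids and CMBs | 2.8 | 2.0 | 2.0 | 4.5 |
| Time trend only | 39.0 | 3.5 | 3.7 | 3.3 |
| Non-lipid dose effect, no trend | 49.7 | 16.8 | 3.5 | 3.7 |
| Trend and non-lipid dose effect | 94.0 | 13.3 | 2.2 | 1.8 |
| Confounder: low lipids, more CMBs | 31.0 | 41.2 | 45.3 | 6.2 |

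With the confounder reversed, no lipids-only run was significantly negative and 32.3% were significantly positive (41.5% with visit, arm and arm-by-visit; 7.2% after baseline lipid). Monte Carlo error on the 39% is √(0.39 × 0.61 / 400) = 2.4 percentage points.

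**Simulation 2.** Independent sets of null runs with accumulating CMB counts, using GEE as the stand-in:

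- Lipids only, baseline included, no time term: a significant association, of negative sign on average, in 100% of 200 runs (exchangeable correlation, grade cut at 3 or more CMBs); negative-sign false positives in 100% of runs at both 0.1 and 0.3 new CMBs per year (exchangeable, 100 runs each); and 98% to 100% in a further set (60 runs per rate).
- The same 0.1 and 0.3 per year settings with independence models: 7% and 24%.
- Arm added without visit: still 98% to 100%.
- Visit added without arm: 2% to 5%.
- Follow-up visits only, no visit term: 0% to 8%, depending on the accrual rate.
- New CMBs per interval on the preceding LDL-C, adjusted for arm, visit, baseline CMB count and baseline LDL-C: 4.5% rejected.

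A mixed model with patient effects relies heavily on within-patient change, where this artefact lies. The exchangeable results are therefore probably the closer guide.

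**The case against.** The strongest counter-argument is that this is a condensed article. Fixed effects, time terms and lags of a mixed model normally sit in a full protocol or SAP that is not shown, and the sentence's reference to time may imply a time term. That stands: the silence is not itself an error, and with a visit term the time artefact disappears.

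The artefact also needs conditions the article does not state. Baseline visits must enter the model, and lipids must actually fall after enrolment. Prior atorvastatin use is not excluded (exclusion 15 covers patients who must use other statins or other lipid-lowering drugs), so not every patient is necessarily starting a statin. That stands too, and it is why the claim is that the model could mislead.

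A reader might infer that the missing arm term causes the artefact. It does not: arm alone leaves the time artefact untouched. Arm matters for a different problem, a non-lipid dose effect, and baseline lipid for a third, patient-level confounding.

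A reader might also infer that the plan gives up randomisation for the second co-primary outcome. The documents do not support that. The chi-square or Fisher's exact comparison by arm is planned separately, on the ITT and PP populations, and the sample-size section frames the primary test as high versus low dose. The lipid model comes after these and is called a correlation.

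What survives is the choice the article does fix: lipid level, not arm, is the explanatory variable in the only repeated-measures CMB model, while the arm comparison gets unadjusted tests.

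**Conclusion.** The point holds as a risk, not a certainty. A lipid-only model with baseline visits and no time term could produce lower lipids with more CMBs when lipids do nothing. Across the simulations with a time trend and no lipid or dose effect, false positives ran from about 39% to 100%, apart from 7% and 24% in one set using independence models. They were near nominal with a visit term, and 0% to 8% with follow-up visits only.

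These figures rest on assumed LDL-C values, CMB accrual rates, grade cut-offs and stand-in models. They show direction and plausibility, not the size to expect in this trial. With no time trend, dose effect or confounder, the false-positive rate is nominal (2.8%), and an opposite confounder reverses the sign.

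The between-arm tests of CMB degree remain valid randomised comparisons. The article does not say that this model will set a lower lipid limit; given how the hypothesis and Discussion are worded, the plan should rule that reading out.

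**What to change.** 1. Analyse the CMB co-primary with a longitudinal model by randomised arm: arm, visit, arm-by-visit and baseline CMB burden as a covariate, with follow-up visits as the outcome. The visit-by-visit chi-square or Fisher's exact tests can stay as description.
2. If the lipid–CMB model is kept, include visit, arm, baseline lipid and baseline CMB burden. Preferably model new CMBs in each interval on the lipid value at the start of that interval.
3. Label that model exploratory and observational, and state that it is not evidence for a lower lipid limit. Adjustment does not make post-randomisation lipid levels a randomised exposure.

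The cost is revised wording and a little more analysis work. Patients, visits, measurements and software are unchanged.
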